# Efficacy and safety of fospropofol disodium sedation for same-day bidirectional endoscopy in elderly patients: protocol for a prospective, single-center, randomized, double-blind, non-inferiority trial

**DOI:** 10.3389/fphar.2024.1378081

**Published:** 2024-08-08

**Keywords:** fospropofol, propofol, sedation, elderly, bidirectional endoscopy

## Abstract

**Introduction:**

Fospropofol disodium is a novel prodrug that has improved pharmacokinetic and pharmacodynamic properties when compared with propofol. This trial aims to compare the efficacy and safety of fospropofol *versus* propofol sedation for same-day bidirectional endoscopy in elderly patients.

**Methods and analysis:**

This is a prospective, single-center, double-blind, randomized, propofol-controlled, non-inferiority trial. A total of 256 patients aged 65 years or older, who are scheduled for same-day bidirectional endoscopy under sedation, will be randomly allocated, in a 1:1 ratio, to either fospropofol group or propofol group (n = 128 in each group). All patients will receive analgesic pre-treatment with sufentanil 5 μg. Two minutes later, an initial bolus dose of fospropofol 6.5 mg/kg or 1.5 mg/kg propofol and supplemental doses of fospropofol 1.6 mg/kg or 0.5 mg/kg propofol will be titrated as needed to achieve target sedation levels during the procedures. The primary outcome is the success rate of same-day bidirectional endoscopy. Secondary outcomes include the time to successful induction of sedation, duration, time to being fully alert, time to patient discharge, endoscopist satisfaction, patient satisfaction, and the top-up frequency and dosage of sedative medications. The safety endpoints consist of adverse events concerning cough reflex, gag reflexes, body movement, muscular tremor, and pain on injection. Sedation-related AEs, including episodes of desaturation, severe desaturation (SpO_2_ < 90%), hypotension, severe hypotension (decrease in MBP ≥30% of baseline), and bradycardia, will also be recorded. Data will be analyzed on an intention-to-treat basis.

**Discussion:**

We hypothesize that the efficacy and safety of fospropofol sedation for elderly patients undergoing same-visit bidirectional endoscopy will not be inferior to that of propofol. Our findings will potentially provide a new sedation regimen for same-visit bidirectional endoscopy in elderly patients.

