### 2.9 Sample size evaluation

The study is designed as a non-inferiority trial with a non-inferiority margin (δ) of 8% in terms of the success rate (Luo et al., 2022; Zhong et al., 2023). At a power of 80%, a one-sided alpha of 0.025, and assuming that the success rate of gastrointestinal endoscopy after fospropofol or propofol administration is both 95%, a total of 234 patients are calculated using PASS software (version 2021, NCSS, United States). Together with an anticipated drop-out rate of 10%, a total of 256 patients (128 patients in each group) will be required for this trial.

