### 2.10 Data management and statistical analysis

Statistical analysis in this trial will be performed using SPSS 25 (SPSS Inc., Chicago, Illinois, United States). Continuous variables are presented as the mean ± standard deviation (SD) or median with the upper and lower quartiles, whereas categorical variables are presented as frequencies and percentages. A P-value <0.05 is considered statistically significant. For the primary efficacy outcome, the difference in gastrointestinal endoscopy success rate between fospropofol and propofol groups and the corresponding two-sided 95% confidence intervals (CIs) will be calculated. Non-inferiority between fospropofol and propofol is concluded if the lower limit of the two-sided 95% CI of the difference in success rate between fospropofol and propofol groups exceeds the non-inferiority margin (−8%). The success rates of gastrointestinal endoscopy will be compared between the fospropofol and propofol groups using the Chi-square test or Fisher’s exact test. The Shapiro-Wilk’s test will be used to assess the data distribution. For comparison of secondary efficacy outcomes, the Cochran–Mantel–Haenszel (CMH) test or Fisher’s exact test will be used to compare the categorical variables between two groups, while a t-test (normal distribution) or Mann-Whitney U test (non-normal distribution) is used to compare continuous variables, as appropriate. The incidence of AEs and drug-related AEs between the two groups will be compared using a chi-square test or Fisher’s exact test. In addition, the further interaction analysis across the subgroups, including age (65–79 years vs. ≥ 80 years), history of cardiovascular, renal, hepatic, and pulmonary diseases (yes vs. no), as well as interventional therapeutic endoscopic procedures (yes vs. no), will be carried out using a logistic regression model to adjust the study outcomes for above-mentioned potential confounding factors. All randomly assigned patients who receive at least one dose of the study medication will be included in the full analysis set (FAS) according to the intention-to-treat (ITT) principle, and at least one evaluable efficacy outcome is used for the analysis of all efficacy outcomes and baseline characteristics of patients. The safety set (SS), which includes all patients based on the “as treated” principle, will be used for the analysis of safety outcomes. Since the anticipated protocol violation will be uncommon and missing data will be supposed to be missing at random, the interim analysis or imputation for missing data are not performed in this trial.

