Fospropofol is a water-soluble, phosphate ester prodrug, which can be metabolized by alkaline phosphatases to release liberated propofol after intravenous administration (Garnock-Jones and Scott, 2010). The released propofol from fospropofol binds to the γ-aminobutyric acid (GABA) receptor and thereby potentiates GABA-inhibitory synaptic currents to induce sedative effects (Garnock-Jones and Scott, 2010). A study of its pharmacodynamic/pharmacokinetic relationship in 12 healthy volunteers found that an intravenous bolus 10 mg/kg dose of fospropofola achieved propofol plasma maximum concentration of 2.2 mg/mLafter 8 (range 4–13) minutes, and reached the minimum mean MOAA/S score of 1.2 after 7 (1–15) minutes. Participants in this study completely recovered from sedation after 21–45 min following fospropofol administration (Bengalorkar et al., 2011). As a new sedative, fospropofol is expected to have the same sedative efficacy as propofol in elderly patients undergoing same-day bidirectional endoscopy, with a lower incidence of adverse reactions caused by hemodynamic and respiratory depression than that of propofol. On bassi of a phase II dose-response trial in patients undergoing colonoscopy, fospropofol 6.5 mg/kg was determined as the ideal dose, as no recorded episodes of deep sedation occurred during procedures under this dose (Cohen, 2008). In addition, both physicians and patients mostly preferred for fospropofol 6.5 mg/kg over the other doses (Cohen, 2008). In two clinical trials, fospropofol was shown to be safe and well tolerated at an initial dose of 6.5 mg/kg intravenously with supplemental doses as moderate sedation for elderly, obese, and high-risk patients in minor surgical procedures (Gan et al., 2010; Bergese et al., 2013). Fospropofol disodium for injection is a prodrug that is metabolized into propofol to produce a general anesthetic effect when administered intravenously. A phase 3 trial demonstrated that fospropofol disodium was not inferior to propofol for general anesthesia induction in American Society of Anesthesiologists (ASA) physical status I-II adult patients undergoing elective surgery and reduced the incidence of pain at the injection site (Wu et al., 2021). In addition, fospropofol’s slower onset should have less impact on patient’s hemodynamics compared to propfol, although it may potentially slow patient recovery (Gan et al., 2010). In clinical conditions where a more prolonged effect is desired and immediate onset of action is less important, fospropofol may have advantages over propofol. A pilot study has shown that fospropofol, administered in either an infusion/bolus or infusion-only regimen, is tolerable and effective for the short-term induction and maintenance of sedation in mechanically ventilated intensive care unit patients (Candiotti et al., 2011). These findings have prompted to exploration of fospropofol in providing sedation for elderly patients undergoing same-day bidirectional endoscopic procedures. However, the role of fospropofol sedation for same-day bidirectional endoscopy in elderly patients has not been fully determined. To our knowledge, this will be the first randomized controlled trial to assess the efficacy and safety of fospropofol sedation for same-day bidirectional endoscopy in elderly patients. In our patients, an initial bolus dose of fospropofol 6.5 mg/kg in combination with sufentanil 5 μg will be used for sedation induction, followed by supplemental doses of fospropofol 1.6 mg/kg as needed to achieve target sedation levels. This strategy will minimize the risk of oversedation and associated complications. Moreover, several confounding factors, which can influence the study outcomes, must be appropriately managed in this study to ensure that the reliable conclusions are obtaine. Subgroup analyses of the efficacy and safety assessments will be performed on basis of age, interventional therapeutic endoscopic procedures, history of cardiovascular, renal, hepatic, and pulmonary diseases.

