
Several limitations must be pointed out in this study. First, our study will specifically include patients aged over 65 years with an ASA physical status I to III and a BMI between 18 and 30 kg/m^2^. Although these inclusion criteria will allow us to evaluate the anesthetic effect of fospropofol in this specific patient population, whether the conclusion from our study can be fully extrapolated to other elderly patients with higher ASA classifications or individuals with obesity warrants further investigation. Second, this trial don’t include different doses in the fospropofol group. We only evaluate 6.5 mg/kg fospropofol in combination with sufentanil for same-day bidirectional endoscopy in elderly patients because we intend to assess the efficacy and safety of fospropofol under the conventional effective dosage on basis of previous studies (Cohen, 2008; Bergese et al., 2013). The next step will be to investigate the dose-response relationship to establish optimal dosage of fospropofol sedation for elderly patients undergoing same-visit bidirectional endoscopic procedures. Finally, this study was a relative small sample, single center trial, and a prospective, multicenter trial with a larger sample size are needed to validate the preliminary results of this study. Despite these limitations, our study will provide valuable insights into the potential benefits of forpropofol-based sedation for same-day bidirectional endoscopy in elderly patients. Further research in larger sample size will be essential to determine optimal dosing regimens and extend the applicability of fospropofol to the broader patient populations undergoing same-visit bidirectional endoscopic procedures.

In conclusion, this prospective, randomized, double-blind, non-inferiority trial will verify the efficacy and safety of fospropofol sedation for elderly patients undergoing same-visit bidirectional endoscopy and confirm whether it is inferior to propofol. We believe that fospropofol represents a new option for sedation of elderly patients during same-visit bidirectional endoscopic procedures.

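### The abstract hypothesises non-inferior safety, but the only margin and decision rule concern the success rate, and adverse events are tested only for a difference

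*Protocol article*

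**What the plan says.** **Hypothesis.** The Discussion paragraph of the abstract reads: "We hypothesize that the efficacy and safety of fospropofol sedation for elderly patients undergoing same-visit bidirectional endoscopy will not be inferior". The comparator is propofol.

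**Expectation.** Section 3 goes further. It expects the same sedative efficacy as propofol, "with a lower incidence of adverse reactions caused by hemodynamic and respiratory depression than that of propofol". That is a superiority expectation for safety.

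**Margin and size.** Section 2.9 sets a "non-inferiority margin (δ) of 8% in terms of the success rate". It sizes the trial on that endpoint alone, using 80% power, a one-sided 0.025 level and an assumed 95% success rate in each arm.

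**Decision rule.** Section 2.10 ties non-inferiority to the lower limit of the two-sided 95% CI for the success-rate difference, set against −8%. It gives no such rule for any other outcome.

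**Safety analysis.** Section 2.6 assesses safety by AE rates and sets no margin. Section 2.10 says: "The incidence of AEs and drug-related AEs between the two groups will be compared using a chi-square test". Fisher's test is the named alternative, and the threshold is P<0.05. The section names a confidence interval for the primary outcome but none for AEs.

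**The concern.** The article contains two safety hypotheses, not inferior in the abstract and better in section 3, and one safety test. A test of equality can support the second if it is significant in the expected direction. It cannot support the first. Non-inferiority needs a stated margin and a confidence limit that excludes it, and failing to reject equality shows neither.

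At stake is the safety conclusion in patients aged 65 and over, whom the Introduction describes as being at increased risk of hypoxaemia and hypotension. With the hypothesis worded as it is and no safety rule beside it, a non-significant AE comparison could be taken as confirming the hypothesis while the data remain compatible with a sizeable excess.

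**Working it through.** **Inputs**
- 128 randomised per arm and 117 evaluable per arm (234/2), one-sided alpha 0.025, power 80%, margin 8 points, success rate 95% in both arms: section 2.9.
- AE tests at P<0.05: section 2.10.
- Propofol event rate of about 30% for desaturation and hypotension: section 3, from earlier endoscopy studies. Treated here as an assumption, with 5% to 40% as an assumed range.
- The fospropofol rates and safety margins below are illustrations. The article gives none.

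**1. The plan's own figure.** n per arm = (1.96 + 0.8416)² × 2p(1−p)/δ². With p = 0.95 and δ = 0.08: 7.849 × 0.095/0.0064 = 116.5, so 117 per arm and 234 in total. The stated 234 reproduces, and it is a calculation for the success rate only.

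**2. Precision for an AE comparison.** Half-width of the 95% CI with the same rate p in both arms = 1.96 × √(2p(1−p)/n).

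| Assumed rate | 128 per arm | 117 per arm |
|---|---|---|
| 5% | 5.3 points | 5.6 points |
| 10% | 7.4 | 7.7 |
| 20% | 9.8 | 10.3 |
| 30% | 11.2 | 11.7 |
| 40% | 12.0 | 12.6 |

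At 30% and 128 per arm: 1.96 × √(2 × 0.3 × 0.7/128) = 0.112. Even identical observed rates would leave an excess of about 11 points inside the interval.

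**3. How often a true excess would be non-significant.** Sum the product of the two binomial probabilities over all 2×2 tables whose uncorrected chi-square gives P>0.05.

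| Propofol vs fospropofol | 128 per arm | 117 per arm |
|---|---|---|
| 30% vs 38% | 0.73 | 0.75 |
| 30% vs 40% | 0.61 | 0.64 |
| 30% vs 45% | 0.30 | 0.34 |
| 5% vs 15% | 0.22 | 0.25 |

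A continuity correction raises these: at 128 per arm, 30% vs 40% becomes 0.66 and 5% vs 15% becomes 0.29.

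**4. One concrete table.** With 35/117 events on propofol (29.9%) and 49/117 on fospropofol (41.9%), the excess is 12.0 points. The uncorrected chi-square gives P = 0.056. The Wald 95% CI is 12.0 ± 1.96 × √(0.299 × 0.701/117 + 0.419 × 0.581/117) = 12.0 ± 12.2, that is −0.2 to +24.2 points. The planned test would be non-significant.

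**5. Would a safety margin be workable?** Use the formula in step 1 with p = 0.30 and an illustrative margin of 10 points: 7.849 × 0.42/0.01 = 329.7, so about 330 evaluable per arm against 117. Margins of 8 and 15 points would need 516 and 147. Power for a 10-point margin at 30% would be 39% with 117 per arm and 42% with 128. Only for events near 5% would 117 per arm suffice for an 8-point margin, and that margin would tolerate a rise from 5% to 13%.

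**The case against.** The strongest reply is that the operative sections agree with one another. The abstract's Introduction states the aim as a comparison, section 2.9 defines non-inferiority by the success rate, section 2.6 measures AE rates and section 2.10 compares them. Explicit non-inferiority of safety appears in one sentence of the abstract, and safety analyses are commonly descriptive. This stands, and it is why the remedy starts with that sentence. It does not remove the mismatch: if safety is descriptive, it does not belong in the non-inferiority hypothesis.

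Four further points limit how far the criticism goes.
- A reader might infer that the investigators intend to take P>0.05 as proof of non-inferior safety. The article never says how a non-significant AE test will be interpreted. The risk is of misreading.
- A reader might conclude that the chi-square or Fisher test is simply the wrong test. It is appropriate for the section 3 expectation of fewer reactions. It fails only for the abstract's hypothesis.
- The closing paragraph of section 3, which says the trial "will verify the efficacy and safety of fospropofol sedation for elderly patients", might be taken as a second claim of non-inferior safety. It does not say so specifically, and the limitations just before it describe a relatively small single-centre sample and call the results preliminary.
- The 30% rate is uncertain. Section 3 does not make clear whether it applies to each event or to both together, or under which definitions. Section 2.6 requires SpO2 below 90% for more than 30 s and hypotension for more than 2 min, so this trial's rates may differ.

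Finally, CIs for AEs may be in an analysis plan that is not shown. Their absence from the article is not itself the fault. They are recommended because they give the reader what the difference test cannot.

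**Conclusion.** The point holds as a mismatch between a stated hypothesis and the stated analysis. As planned, the trial can test whether AE rates differ, but it cannot establish that safety is not inferior. The abstract and section 3 also express different safety hypotheses that need reconciling.

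The size depends on the event rate. If it is near 30%, differences of about 11 points either way are compatible with equal observed rates, and a true 10-point rise would usually be missed (61%). If it is near 5%, precision is about 5 points and the same absolute rise would be missed in roughly one trial in five (22%). Both rates are assumptions; these figures use 128 per arm, and 117 per arm is slightly worse.

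The documents do not support saying that the investigators will declare safety non-inferior on a non-significant test. The sample size, the primary analysis and its decision rule are untouched. The correction should be made, but it concerns what may be claimed about safety rather than the validity of the primary result.

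**What to change.** 1. In the abstract's Discussion paragraph, limit the non-inferiority hypothesis to the success rate. State the safety aim separately and make it consistent with the expectation in section 3.
2. In section 2.10, report the main sedation-related AEs (hypoxia, hypotension and bradycardia, as defined in section 2.6) as risk differences with 95% CIs beside the planned tests.
3. In section 2.10, state that P>0.05 for an AE comparison will not be described as non-inferior or equivalent safety.

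Do not add a safety non-inferiority margin to this trial. For events near 30%, a 10-point margin needs about 330 evaluable patients per arm, and the rates under this trial's own definitions are not known in advance. The description in section 3 of the trial as assessing efficacy and safety can stay.

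The cost is a few sentences and three intervals computed from data already collected. No patients are added and the primary analysis does not change. The downside is a more modest safety claim.

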**Clinical Trial Registration:**

clinicaltrials.gov, identifier NCT02875639

## 1 Introduction

With life expectancy rising around the world, the incidence of gastrointestinal diseases increases in parallel with the aging of population. Research statistics indicate that elderly people account for a high proportion of all newly diagnosed gastrointestinal malignancies (Hall et al., 2005). Gastrointestinal endoscopy is an effective diagnostic method for gastrointestinal diseases. Same-day bidirectional endoscopy (esophagogastroduodenoscopy and colonoscopy) has become increasingly common due to its cost-effectiveness and ability to enhance decision-making (Urquhart et al., 2009). Recent studies have shown that the optimal sequence for patients undergoing same-day bidirectional endoscopy under sedation is esophagogastroduodenoscopy followed by colonoscopy (Laoveeravat et al., 2020).

Moderate sedation is necessary during gastrointestinal endoscopy to reduce the patient’s memory of the event, make them more comfortable and less anxious, and significantly improve the procedure outcome (Early et al., 2018; Zhou et al., 2021). Though the types of medications used for sedation in elderly patients are not different from those in younger patients, it is important to be aware of the increased sensitivity of this population to sedative medications (Chandrasekhara et al., 2013). Elderly patients are at increased risk for adverse events, such as hypoxemia, hypotension, arrhythmias, and esophageal reflux during the gastrointestinal endoscopy (Laanani et al., 2019; Shimizu et al., 2021). Therefore, clinicians should pay more attention when administering sedative medications to elderly patients undergoing gastrointestinal endoscopy. Over the long term, propofol is the most commonly used sedative agent for gastrointestinal endoscopy due to its rapid onset of action and fast recovery (Zhang et al., 2018). Propofol combined with opioids has become the most common regimen of sedation in China (Zhou et al., 2021). However, due to its narrow therapeutic window, propofol poses high risks of adverse events such as respiratory depression, hypotension, and pain on injection, especially in elderly patients (Shimizu et al., 2021).

Fospropofol disodium for injection (manufactured by Yichang Human well Pharmaceutical Co., Ltd., Hubei, P. R. China) is a novel water-soluble prodrug of propofol. It has a unique pharmacokinetic and pharmacodynamic profile compared to lipid propofol (Wu et al., 2021). As a prodrug of propofol, fospropofol’s pharmacologic activity results from its breakdown by alkaline phosphatase and subsequent release of propofol (Liu et al., 2020). Compared to propofol lipid emulsion, it exhibits a longer time to peak clinical effect and a more prolonged action, resulting in smoother hemodynamic and respiratory depression in patients (Abdelmalak et al., 2012). Additionally, it does not cause a burning sensation upon IV administration, which is a common side effect of propofol (Garnock-Jones and Scott, 2010). The available evidence suggests that fospropofol sedation is effective for patients undergoing esophagogastroscopy, colonoscopy, and flexible bronchoscopy (Cohen et al., 2010; Gan et al., 2010; Bergese et al., 2013; Wu et al., 2021). Despite these promising findings, the optimal sedation regimen for fospropofol to facilitate same-day bidirectional endoscopic procedures remains unclear. Moreover, it is worth noting that most studies have been conducted on populations with a wide age range and have not investigated the safety of fospropofol in elderly patients (Abdelmalak et al., 2012). As a result, we designed this study to evaluate the efficacy and safety of fospropofol in comparison with propofol for sedating elderly patients undergoing same-day bidirectional endoscopy.

